#### Randomization

Recruitment will begin on June 1, 2021. After screening the adolescents and having eligible adolescents complete the questionnaires, randomization will be conducted. This study is a two-group, parallel, single-blind randomized controlled trial with a sample size of 206 adolescents. From a total of 25 schools, 8 schools will be randomly selected by simple randomization methodology. A list of schools will be provided by referring to the Department of Education. All high schools will be considered eligible to have the opportunity to reach students of all different socioeconomic levels. After checking the eligibility of the adolescents, of the 206 participants’ schools, 103 adolescents will be randomly assigned to the intervention group, and the other 103 adolescents randomly assigned to the active control group by simple randomization methodology. The simple randomization will be done to assign participants for study groups by an independent statistician with a 1:1 allocation.

From each school, the students selected will receive a special code through SPSS software, and after analyzing the data, they will be selected randomly through these codes.

Blindness will not be performed in study participants due to the different natures of the approaches in the active control and intervention groups, with one group receiving educational training on IGD and the other receiving educational information on sleep hygiene. Study administration and the statistician will be blinded to group allocation.

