**Fig 1 Fig1:**
[figure not shown]
CONSORT flow diagram

In order to select the sample, a one-stage sampling method will be used. For this purpose, a list of secondary schools will be prepared. Then, out of 25 high schools, 8 will be randomly selected and screened for gaming disorder in all students who play computer games (both online and offline) using the nine-item Internet Gaming Disorder Scale - Short Form (IGDS-SF9). An online questionnaire will be provided to adolescent students through school information channels so that those who volunteer may participate in this research. Eligible adolescents (*n* = 206) will be randomly assigned into action control (*n* = 103) and intervention groups (*n* = 103). An online questionnaire will be provided to adolescent students through school information channels so that those who volunteer can participate in this research.

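### The stated simple randomisation does not guarantee the stated 103:103 split and leaves balance across the eight schools uncontrolled; use blocks stratified by school and treat 103 as a target

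*Protocol article*

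**What the plan says.** The Randomization section describes a "single-blind randomized controlled trial with a sample size of 206 adolescents". It fixes the arm sizes: "103 adolescents will be randomly assigned to the intervention group, and the other 103 adolescents randomly assigned to the active control group", and the same sentence names simple randomisation as the method, the second group being "randomly assigned to the active control group by simple randomization methodology". The next sentence repeats it: "The simple randomization will be done to assign participants for study groups by an independent statistician with a 1:1 allocation". The Study design section gives the same sizes; eligible adolescents "will be randomly assigned into action control (*n* = 103) and intervention groups (*n* = 103").

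On timing: "After screening the adolescents and having eligible adolescents complete the questionnaires, randomization will be conducted". On schools: "From a total of 25 schools, 8 schools will be randomly selected by simple randomization methodology". A separate sentence then says: "From each school, the students selected will receive a special code through SPSS software", and goes on to say that, once data have been analysed, students are picked at random by these codes.

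The article describes no block, stratum or other restriction. The Statistical analysis section plans a two-level mixed model for repeated measures on adolescents, with no school level or school term.

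**The concern.** Simple randomisation normally means that each participant is assigned independently, like a coin toss. That fixes the chance of each arm, not the number in it. The article therefore names a method and promises a result that the method does not ensure. The sentence on codes adds to the doubt: it does not say what is being selected, which data are analysed first, or whether the draw is made within each school or over all 206. As written, the allocation could not be reproduced.

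Individuals from eight schools are randomised after screening and baseline questionnaires, so each participant's school can be known before allocation. Nothing keeps the arms balanced within schools, and the model does not adjust for school. At stake are a clear allocation rule and a small amount of precision, not the validity of the comparison.

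**Working it through.** **Inputs from the protocol article.** Total 206, 103 per arm, 1:1, simple randomisation, 8 schools (Randomization); d = 0.50, power 90%, significance level 0.05, about 20% loss (Sample size/power calculation). **Assumptions.** Two-sided test; school sizes, school ICC, block size and baseline correlation as given in each step, since the article gives none of them.

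**1. The stated 103.** A two-sided two-sample t-test at d = 0.50 and 90% power needs 85.03, so 86 per arm. 86 × 1.20 = 103.2, which matches 103. The figure is thus a planned number per arm, not a product of the allocation method.

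**2. Arm sizes under independent assignment.** X ~ Binomial(206, 0.5).
- P(X = 103) = 0.0555, or 5.6%.
- SD of the difference between arms = √206 = 14.4.
- P(89 ≤ X ≤ 117) = 0.957.

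**3. Cost in power.** Relative efficiency at 89:117 is 4 × 89 × 117 / 206² = 41,652 / 42,436 = 0.982.

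| Split | Power, all 206 analysed | Power, 80% retained |
|---|---|---|
| 103:103 | 94.6% | 89.1% |
| 89:117 | 94.3% | 88.5% |

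Averaged over all splits, power under simple randomisation is 94.5% and 88.9%.

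**4. Balance within schools.** With 206/8, about 26 per school, the chance of 9:17 or worse in one school is 2 × P(Binomial(26, 0.5) ≤ 9) = 0.169. For at least one of eight it is 1 − (1 − 0.169)^8 = 0.772. Simulation with six schools of 26 and two of 25 gives at least one school at 35:65 or worse in 74% of runs under simple randomisation, and in 64% under a single draw of 103 codes. With uneven schools (assumed 60, 45, 30, 25, 18, 13, 9, 6) the figures are 94% and 92%, where small schools reach such a split easily. Fixing the overall total therefore does little for school balance.

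**5. What stratifying and adjusting gains.** On a unit-variance scale, the unadjusted variance of the treatment difference is ICC × w + (1 − ICC) × v. Here w is the mean sum of squared differences between the arms' school proportions, and v is the mean of 1/n₁ + 1/n₂. The simulation (schools of 25 or 26, simple randomisation) gives w = 0.01717 and v = 0.01951. With school balanced and in the model, the variance is (1 − ICC) × 4/206. Both are shown relative to 4/206 = 0.01942.

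| Assumed ICC | Unstratified, unadjusted | Stratified, adjusted | Reduction |
|---|---|---|---|
| 0.01 | 1.004 | 0.990 | 1.4% |
| 0.05 | 0.999 | 0.950 | 4.9% |
| 0.10 | 0.993 | 0.900 | 9.4% |

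Against a single draw of 103 codes the reduction is 0.9% (1 − 0.990/0.9988) to 8.9% (1 − 0.900/0.9880).

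Baseline is one of the modelled time points and already carries part of any stable school difference. With baseline adjustment, stable school effects and baseline–follow-up correlation r, the gain is about ICC × (1 − r)/(1 + r). At an assumed r = 0.5 the factor is 0.5/1.5 = 1/3, so the gain is about 0.3% at ICC 0.01 and 3.3% at ICC 0.10.

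**6. What the remedy does to the split.** Permuted blocks of 4 within schools of 25 or 26 keep each school within a difference of 2. The overall split is exactly 103:103 in only about 25% of runs (mean absolute difference 2.5, largest seen 12). Blocking within school controls balance but does not force the exact total.

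**The case against.** The strongest reply is that the text allows a fixed-size draw. Randomisation follows screening and baseline, 103 are assigned and the remainder form the other arm, and students are picked by code. Drawing 103 of 206 codes at once gives 103:103 exactly. Equally, 103 may be only a target. This stands: a reader might infer that the stated method cannot produce the stated split, and the document does not support that. It supports only that the split is not guaranteed, or else that the label is wrong.

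It also stands that unstratified individual randomisation of 206 people is valid. A reader might infer that chance imbalance between schools biases the comparison. It does not, and the 77% in the working describes an uneven split in some school, not harm to the treatment estimate. A reader might also take school as an established prognostic factor. The article says only that all schools are eligible, so that students of different socioeconomic levels can be reached; nothing in it links school to the IGDS-SF9.

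Finally, a reader might infer from the sentence on codes that allocation depends on analysed results. The wording is more likely awkward phrasing for processing screening data or for sampling within schools. It should be clarified, not simply deleted, since it is the article's only account of the code-based mechanism.

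The reply does not reconcile the label with the fixed arm sizes, and it leaves school balance uncontrolled on either reading. That the article condenses a fuller protocol is no answer, because it names the method twice.

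**Conclusion.** The concern holds in a limited form. Simple randomisation and exactly 103 per arm do not fit together as written: under independent assignment the exact split has probability 5.6%, and under a single draw of codes the word simple is wrong. The sentence on codes does not resolve which is meant. The effect on power is negligible, about 0.3 percentage points at 89:117 with all analysed and 0.6 at 80% retention, and there is no bias.

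Balance across the eight schools is uncontrolled, and school is absent from both the allocation and the model. Correcting this yields a small gain, about 1% to 9% of the variance of the treatment difference for ICCs of 0.01 to 0.10 before baseline is taken into account, and less after. The gain rests on assumed ICCs and assumed school sizes; the 5.6% rests only on 206 and independent 1:1 assignment. The change is worth making because it replaces an inconsistent rule at almost no cost, not because the trial is at risk without it.

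**What to change.** - Replace simple randomisation with a concealed, computer-generated list from the independent statistician, in permuted blocks of varying size, 1:1, stratified by school.
- Describe 103 per arm as a target, in both Randomization and Study design, since blocking within school does not force an exact total.
- Rewrite the sentence on codes to say what is drawn, from which list, at what point, and what analysis (if any) precedes it.
- Add school as a fixed effect to the model, to match the stratification.

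If stratification is not wanted, the least that removes the inconsistency is to state a single draw of 103 from 206 codes and drop the word simple; school balance then stays uncontrolled.

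**Cost.** One different list from the same statistician, seven degrees of freedom for eight schools, and slight predictability of assignments, limited by varying the block sizes. Recruitment, visits and outcomes do not change.

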### Study interventions

#### Intervention condition

The TTM model consists of six domains including (1) stages of change, (2) process of changes, (3) decisional balance, (4) change level, (5) self-efficacy, and (6) temptation. In this study, we will focus on three domains, as described below. The first domain is stages of change. While changing behavior and achieving the desired behavior, it is important to consider different stages [27]. In the first stage (Stage 1: Precontemplation), due to lack of awareness or knowledge or experiences of failed attempts to change in the past, the person may not have enough motivation to consider behavioral change during the next 6 months. In the next stage (Stage 2: Contemplation), the person has the necessary knowledge regarding the results of performing the desired behavior and knows the benefits of performing the behavior and the costs of performing the behavior, but he/she may not have self-confidence or motivations to make changes in behavior during the next 6 months. In the third stage (Stage 3: Preparation), people may analyze more fully costs and benefits in performing the behavior. People in this stage value the benefits more than the obstacles, and by planning for the next 30 days, they typically feel one step closer to their goals. After the preparation stage, the person may be better able to resist temptations and persevere to adopt the new behavior. In the next stage (Stage 4: Action), a new behavior may be adopted by the person within the next 6 months. In the next stage (Stage 5: maintenance), positive changes in his/her lifestyle have typically occurred, and he/she has experienced a change in behavior for at least 6 months and a maximum of 5 years with more confidence and less temptation. The risk of unusual temptations and the consequences of false self-confidence may still precipitate relapse.

The second domain of the TTM model involves processes of changes. These processes include overt and covert activities that a person may use to progress through the stages of change. In other words, these include any activities that a person does to help modify the way he/she thinks, feels or behaves.

The next TTM domain considered is decisional balance. Decision-making is the process by which an individual considers the outcome of mental agreements (positive mental images, values, and beliefs) and oppositions to engage or not in behaviors. This domain is similar to that of perceived benefits and barriers in the health belief model [56]. The balance between perceived agreements and disagreements often fluctuates throughout stages of change.

Self-efficacy is the third domain considered for the intervention group. This domain, which comes from Bandura's theory of social learning, is a person’s self-efficacy and has a linear and positive relationship with the domain of stages of change. If a person goes to higher stage of change, his/her self-efficacy also increases [57].

The present study will focus on three domains of the TTM model (i.e., stages of change, self-efficacy and decision balance) in order to investigate the role of the TTM model in the treatment of IGD. One of the reasons for selecting these three domains is their success in statistically predicting individuals’ addictive gaming behaviors, which has been examined and demonstrated in a previous study [58].

Beside the TTM model, CBT will be used for our intervention. CBT is a form of psychotherapy that helps people understand thoughts and feelings that influence their behaviors. During treatment, a person learns how destructive or disturbing thoughts may have negative effects on their behaviors [59], and they may learn coping skills to manage their thoughts and feelings in a more healthy fashion [30].

After installing the app, each individual enters into the study with a use code that can be a mobile phone number or email that is recorded in the initial screening of each person in the study. Thereafter, a confirmation code is received via SMS.

The main page of the app consists of 4 sections: 1. content of training sessions, 2. exercises and weekly assignments, 3. questionnaires, and 4. a progress chart. The trainings are designed for 8 consecutive weeks (one session per week), and the approximate duration of each session is 30 min. Training includes written texts, videos, and audio files (relaxation music, relaxation exercise, and audio stories). Table 1 provides an overview of the content of each session in the intervention group (Screenshots of the app is provided in Additional file 1).

**Table 1 Tab1:** Intervention content for the intervention group, based on cognitive behavioral therapy (CBT)

Session	Content
First	Introduction of the program, definition of IGD, types of video games, comparison of the prevalence of the disease in Iran and the world, consequences of online games, review of diagnostic criteria for online gaming disorder
Second	Learning to communicate with others, listening skills, bad communication characteristics, secrets of effective communication, teaching mindfulness, friendship and kindness, motivational video, homework presentation
Third	Identifying negative thoughts, replacing realistic thoughts, the impact of thoughts on emotions, learning coping skills with negative thoughts, video lectures, homework presentation
Fourth	Relationship between stress and IGD, definition of stress, types and symptoms of stress, identifying stressors, positive and negative strategies for coping with stress, video lectures related to the session and learning to breathe properly, audio story, homework presentation
Fifth	Relaxation training, mindfulness training, body scan and breathing along with audio files
Sixth	Review of past sessions, familiarity with the importance of problem solving, teaching problem solving techniques, motivational videos
Seventh	Review of past sessions, prevention of relapse, training to adopt a healthy lifestyle, providing solutions to prevent relapse of IGD, video lectures related to the session, homework presentation
Eighth	Summarize the content along with an overview of all past sessions

The training time for each person is counted through the app from the day the sessions start until the content of the next session is activated, which is 7 days later. A reminder message will be sent to each participant to announce each new session. The content of the sessions includes raising awareness and examining the impact of online gaming on people's physical and mental health. It also identifies and corrects misconceptions about online games. This training also includes learning self-control, coping responses, and how to overcome temptation.

The third part of the app includes questionnaires. Participants will answer questions at baseline, 1 month, and 3 months after the end of intervention.

The fourth part of the app aims to evaluate the effectiveness of the intervention in each session according to the weekly completion of the IGDS-SF9 incorporated into exercises and assignments. Participants can monitor their progress in the chart.

Behavior-change interventions are usually complex, complicating research efforts and implementation of practical applications. A method proposed by Michie et al. characterizes the reliability of interventions in terms of behavior change techniques (BCTs) [60]. BCTs are defined as visible, reproducible, and integral components of an intervention designed to change behavior. BCTs can be used alone or in combination and in different forms. We will use BCTs in intervention group to increase effectivity. Several BCTs have been used for this intervention in the app during each session. These BCTs are summarized in the Table 2.

**Table 2 Tab2:** Defined behavior change techniques (BCTs) with links to objectives for the intervention group

BCT number	Name	Description
1.2	Problem solving/coping planning	In the content of the sixth session, it will be discussed that adolescents should make a list of problems that may occur during the day and even imagine the problems they are currently facing. They will be then instructed to choose the problem that is most important to them and define it clearly for themselves (for example: excessive use of online games). They will be then instructed to think about the consequences that playing online games has had on their health, or has changed their behavior with those around them, or has led them to stay up late at night. They will be then instructed to make a list of these and look for solutions to reduce time spent gaming, listing what comes to mind, how they can control their gaming time, and then finding solutions that they find desirable and easy to implement.
1.4	Action planning	In the sixth session, the importance of management of time spent playing online games will be discussed. Adolescents will receive instruction regarding how to manage their intention to keep their gaming time low, with a focus on making decisions about durations, locations and plans for reductions in gaming. The adolescents will be encouraged to decide how they will do this.
2.3	Self-monitoring of behavior	In the app progress chart section, from the first to the eighth week, adolescents will be asked to complete a 9-question Internet Game Disorder Questionnaire on weekly basis. The total score of the questionnaire will be presented in a graph. They will be able to see their progress on a weekly basis based on the answers provided and points they receive.
4.1	Instruction on how to perform a behavior	In all sessions, training regarding communication skills (the second week), identifying negative thoughts, effects of thoughts on emotions, learning alternative behaviors (the third week), stress management (the fourth week), and training in coping skills (the seventh week) will be used. For example, in the fifth week, relaxation techniques constitute one of the trainings used for participants to reduce stress and improve self-efficacy to overcome excessive use of online games.
5.1	Information about consequences	In the first week, a session will describe consequences of IGD on physical and mental health, resulting behavioral problems and financial costs that these games may create for adolescents.
5.4	Monitoring of emotional consequences	In the third week, participants will be informed about their situation by challenging their negative thoughts with a series of questions. Logical and useful alternative perspectives that they may adopt will be provided. Participants will be asked to write down events that they experience during the week according to the approach they have learned in the exercises section.
8.1	Behavioral practice/rehearsal	At the end of each session, adolescents will be asked to do their homework by referring to the exercises related to each session to stabilize their behavior to perform a new activity and observe a change in their behavior in the long term.
9.1	Credible source	Depending on the topic of each session, we will use the best and most expressive videos and music that emphasize the promotion of that behavior. In week 2, we will use the motivational video “Say Thank You.” In the fourth week, we will use a clip entitled, “The impact of stress on the body.”
9.2	Pros and cons	Outline the potential risks of problematic gaming (e.g.. neuroticism, aggression and hostility, sensation seeking, and attention deficit hyperactivity disorder). The adolescents will be asked to list the potential risks of problematic gaming and the potential benefits of non-problematic gaming (e.g., healthy brain stimulation)

The use of TTM model constructs in the intervention content of the HAPPYTEEN app is as follows:

##### Stages 1 and 2: Precontemplation and contemplation

The app intervention has been personalized based on the adolescent’s place in stages of change. For example, for those adolescents who are identified in precontemplation (Stage 1) and contemplation (Stage 2) stages, the app will direct them to start the intervention from session 1. In the stages of precontemplation (Stage 1) and contemplation (Stage 2), the aim is to help adolescents gain a better understanding of the definition of IGD and statistics on studies of IGD in Iran and globally. The prevalence of IGD and the similarity of IGD with substance use disorders will be comprehensively described to the adolescents. Moreover, an explanation about the positive and negative consequences of online games on people’s health will be described.

